**Assessment index**								
Blood test	√					√		
ECG	√					√		
Urine test	√					√		
MRI	√					√		
X-ray	√					√		
JOA	√	√	√	√	√	√	√	√
ODI	√	√	√	√	√	√	√	√
VAS	√	√	√	√	√	√	√	√
SF-12	√	√	√	√	√	√	√	√
Adverse event		√	√	√	√	√	√	√

The “√” represents the implementation.

ECG = electrocardiogram, MRI = magnetic resonance imaging.

#### 2.8.3. Visit plan.

In this study, 8 visit points were designed (see Table 1), including day 0 before treatment (baseline, V1) and 5 visit points during 14 days of treatment (V2 ~ V6). The follow-up time points include month 1 (V7) and month 3 (V8). Each patient will complete all visits on the 3rd month. JOA, ODI, VAS, SF-12 scores will be collected at all interview points. Blood test, urine test, ECG, MRI, and X-ray will be collected at baseline and at the end of the treatment period on day 14. Adverse events (AEs) will be collected at all visit points (V2 ~ V8) during treatment and visit.

### 2.9. Safety assessment

The incidence of AEs was used to assess the safety of the intervention. The AEs of all patients were collected during treatment and follow-up, and the severity of AEs was evaluated. We will report the AEs to the ethics committee, which will decide whether to terminate the trial. The patient’s AEs will be recorded in detail in the case report form for the evaluation of the final results. If the patient has AEs, this study will bear all the medical expenses of the patient to adverse reactions.

### 2.10. Data collection and management

This trial uses a paper-based case report form (CRF) and an electronic data management system. The study staff will collect basic subject information, observational indicators, laboratory indicators, and AEs. Data collators will fill in the above data in the case report form and study medical record.

### 2.11. Statistical analysis

All outcomes were analyzed based on intention-to-treat analysis. The analysis will be carried out with SAS 9.3 software. It is statistically significant that the *P* value of bilateral test is less than 0.05. Multivariate imputation by chained equations method will be used for analysis and data processing of those who violated the trial protocol. Data analysis will be conducted by independent statisticians.

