### 2.7. Sample size

This study is a randomized controlled trial with parallel control and superiority design. According to previous literature, the VAS score of the control group (celecoxib capsule) after treatment was 5 points.^[22–27]^ It is expected that after 2 weeks of treatment, the difference between the experimental group (Yaobitong capsule) and the control group is 0.5 points, and the standard deviation of the 2 groups is the same (standard deviation = 1.1). It was hypothesis *α* = 0.05 (bilateral), 1-*β* = 0.90. According to the calculation of PASS 11 software, at least 206 cases were collected in this study. Assuming a loss of follow-up rate of 20%, 258 patients need to be included in this study.

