### 2.8. Outcome measurements

#### 2.8.1. Primary outcome.

VAS (visual analogue scale) score of leg pain on the 14th day of treatment was the main evaluation index of curative effect. VAS adopts a 10 cm scale divided into 1 to 10 points, of which 10 points are the maximum pain and 0 points are painless.^[28]^ Patients choose the score according to the degree of leg pain, which is the VAS score to evaluate the degree of pain.

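### Section 2.11 aims imputation at protocol violators instead of missing values, and so permits replacement of recorded outcomes under an intention-to-treat label

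*Protocol article*

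**What the plan says.** Two statements stand close together in section 2.11 of the protocol article.

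- The analysis principle: "All outcomes were analyzed based on intention-to-treat analysis".
- The only imputation rule in the article: "Multivariate imputation by chained equations method will be used for analysis and data processing of those who violated the trial protocol".

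The section does not define a protocol violation. It does not mention missing values, and it does not say that any recorded value is to be deleted or set to missing.

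The outcome most exposed is the primary one in section 2.8.1: "VAS (visual analogue scale) score of leg pain on the 14th day of treatment was the main evaluation index of curative effect". Section 2.7 plans on the basis that "the difference between the experimental group (Yaobitong capsule) and the control group is 0.5 points" with "standard deviation = 1.1" in each arm. The Discussion (section 3) lists as a limitation that participants and outcome assessors are not blinded.

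**The concern.** Violation and missingness are different things. A patient who departs from the protocol may still attend on day 14 and give a VAS score. Intention-to-treat requires that score to be analysed in the randomised arm. A patient who follows the protocol may still have a missing score. A rule that attaches imputation to violators therefore has the wrong target in both directions.

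For a violator with complete data, the sentence has an effect only if the recorded score is first set to missing and then filled by a model. If the model learns mainly from adherent patients, the result moves towards what would have been seen had everyone complied. That is a different quantity from the one the section promises.

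The direction of the harm depends on who violates. It is plausible, though not documented, that patients with poor pain relief deviate more often. If so, replacing their scores with predictions from adherent patients flatters the arm with more treatment failures. Where patients and assessors know the treatment and the two regimens differ, equal violation in both arms cannot be taken for granted. Because a violation is not defined, the choice of whose values to model could also be made after the data are seen.

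**Working it through.** **1. The plan's own figure.** Inputs from section 2.7: difference 0.5, SD 1.1, two-sided alpha 0.05, power 0.90.

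- Normal approximation: n per arm = 2 × (1.960 + 1.282)² × 1.1² / 0.5² = 101.7, rounded up to 102, or 204 in total.
- Two-sample t-test: 102.7 per arm, rounded up to 103, or 206 in total. This matches the plan.
- Allowance for 20% loss: 206 / 0.80 = 257.5, rounded up to 258. This also matches.

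The sample size is sound on its stated inputs, and nothing below changes it.

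**2. The two statements set side by side.**

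| Patient | Intention-to-treat | Imputation sentence, read literally |
|---|---|---|
| Adherent, day-14 VAS recorded | use recorded value | not covered |
| Violator, day-14 VAS recorded | use recorded value | processed by imputation |
| Violator, day-14 VAS missing | needs a missing-data method | processed by imputation |
| Adherent, day-14 VAS missing | needs a missing-data method | not covered |

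The conflict is in the second row. The fourth row shows the mis-targeting, but the lack of a rule for it is not a defect in a condensed article.

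**3. How many patients could be affected.** The article gives no violation rate. At assumed overall rates of 5%, 10% and 20%, the numbers are 258 × 0.05 = 13, 258 × 0.10 = 26 and 258 × 0.20 = 52 (rounded).

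**4. Worst case, violators in one arm only.** Assume no true difference and 129 patients per arm. A fraction v of one arm violates, and their true scores are d points worse than the imputed ones.

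- Bias = v × d.
- SE = 1.1 × √(2/129) = 0.137.
- Type I error = P(|N(bias/SE, 1)| > 1.96).

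| v | d | Bias | Bias / 0.5 | Bias / SE | Type I error |
|---|---|---|---|---|---|
| 10% | 1.0 | 0.10 | 20% | 0.73 | 11.3% |
| 10% | 1.5 | 0.15 | 30% | 1.10 | 19.5% |
| 10% | 2.0 | 0.20 | 40% | 1.46 | 30.9% |

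This SE treats all 258 patients as contributing full information. With the information of only 103 per arm, SE = 1.1 × √(2/103) = 0.153, and biases of 0.10 and 0.20 give 10.0% and 25.7%. The exact percentages depend on this choice. The inflation above 5% does not.

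**5. Milder case.** Assume adherent patients differ by the planned 0.5 and that a fraction v of the Yaobitong arm violates and does no better than control. The difference with scores used as observed is (1 − v) × 0.5. Imputing those patients as if adherent restores about 0.5.

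| v | As observed | Imputed as if adherent | Overstatement |
|---|---|---|---|
| 5% | 0.475 | 0.50 | 0.025 |
| 10% | 0.45 | 0.50 | 0.05 |
| 20% | 0.40 | 0.50 | 0.10 |

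The overstatement is 5% to 20% of the planned difference.

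**6. Violation in both arms.** With fractions v₁ and v₂ and shortfalls d₁ and d₂, bias = v₁d₁ − v₂d₂. If the two products are equal, the bias is zero. Only imbalance distorts the comparison.

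**The case against.** The strongest reply is that a compatible reading exists. Chained equations fill only empty cells. Replacing a recorded score needs a prior step that blanks it, and section 2.11 contains no such step. Read together with the intention-to-treat commitment, the sentence may mean only that patients who deviated or withdrew stay in the analysis and have their missing values imputed. An undefined term such as protocol violation could include patients who stop attending.

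This stands as far as it goes. A reader might infer that observed outcomes will be replaced and that intention-to-treat is therefore not delivered; the text does not establish either. The benign reading does not rescue the wording, however. The sentence never mentions missing values, and it applies imputation to violators as a class. A rule that supports two different primary analyses does not fix one.

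A reader might also infer that the 20% planned as lost to follow-up are wrongly left without a method. That is not supported. A condensed article may leave missing-data handling to the full protocol or analysis plan. The 20% is also a planning allowance with no visit attached: follow-up runs to month 3 while the primary outcome is at day 14, so it is not a count of missing day-14 scores.

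The size is also open to challenge. Placing all violators in one arm, 1.0 to 2.0 points (about 0.9 to 1.8 SD) worse than imputed, is severe. VAS scores from days 1, 3, 5 and 7 could enter the imputation model and narrow the gap between true and imputed values. Variance between imputations would raise the standard error and lower the quoted error rates. These points stand, so the worst case is a bound under stated assumptions and not a forecast.

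**Conclusion.** The point holds as a badly fixed rule: the imputation sentence names the wrong target and, as written, permits or implies replacing violators' recorded outcomes with modelled ones. It does not show that this will be done. It is more than missing detail, because an analysis plan that followed the sentence literally would depart from intention-to-treat, and one that kept to intention-to-treat would have to depart from the sentence.

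The possible effect on the day-14 comparison runs from close to nothing, if violation is balanced, through the milder range in the working, to the one-arm worst case there. All of these rest on assumed violation rates and assumed shortfalls. The wording should be settled before the analysis, because it determines what the primary result estimates.

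**What to change.** Replace the imputation sentence in section 2.11 with wording such as: *All randomised patients are analysed in their assigned group; observed outcomes are used as recorded whatever the adherence or protocol violation; multiple imputation by chained equations is used only for missing outcome values.*

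If an analysis that removes or replaces violators' data is also wanted, label it per-protocol or hypothetical, and supportive. The choice of imputation model, its auxiliary variables and any sensitivity analysis belong in the analysis plan and need not be added here.

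The cost is one rewritten sentence. No new data are needed, and the 206 and 258 stay as they are.

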## 3. Discussion

Conservative therapy is the first choice for patients with acute low back pain. Some studies pointed out that physical therapy such as traction, laser, and ultrasound can effectively treat acute LDH, which may provide effective external therapy for patients in the acute stage.^[15,32]^ Although some clinical guidelines highly recommend nonsteroidal anti-inflammatory drugs such as celecoxib and ibuprofen as first-line drugs to low back pain, Yaobitong, ^[9,27]^as a Chinese patent medicine, has been widely used in the clinical treatment of low back pain in China.

Yaobitong capsule contains Panax notoginseng, Ligusticum chuanxiong, Rhizoma Corydalis, Radix Paeoniae Alba, Achyranthes bidentata, Cibotium barometz, cooked Rhubarb and Angelica pubescens.^[33]^ Traditional Chinese medicine believes that Yaobitong capsule has the effects of promoting blood circulation, hemostasis, detumescence, and analgesia, and can effectively treat patients with acute low back pain. Recent studies on the determination of rat plasma components found that the Yaobitong capsule mainly contains ginsenoside Rg1, ginsenoside Rb1, osthol, tetrahydropalmatine, paeoniflorin, paeoniflorin, and ferulic acid, among which the content of ginsenoside from Panax notoginseng is the highest,in recent years, Ginsenoside Rg1 and ginsenoside Rb1 are considered to be effective components for the treatment of LDH.^[34]^ Previously, several randomized controlled trials showed that oral Yaobitong capsule could significantly reduce VAS score, IL-1β and TNF- α in serum, the total effective rate of LDH is more than 95%.^[35–37]^However, the intervention of these trials adopted the scheme of Yaobitong combined with other therapies (e.g., traction, acupuncture). At present, there is deficient evidence of efficacy on the alone application of Yaobitong capsule.

Overall, the current evidence shows that oral Yaobitong capsules have a good effect on LDH, but this conclusion is not confirmed by large sample randomized controlled trials, especially in the treatment of acute LDH. The purpose of this study is to further explore the efficacy and safety of Yaobitong capsules in the treatment of acute LDH and to provide reference evidence for health decision-making. Referring to the guidelines on low back pain, we developed a control group celecoxib, which is recommended as a first-line treatment for acute low back pain. We adopted internationally recognized efficacy measurement methods, including VAS, JOA, ODI, and SF-12 scale. The lumbar dysfunction, degree of pain, and quality of life of all participants will be assessed by these scales. In addition, based on the large sample study of 258 patients, we can explore adverse reactions and safety indexes of Yaobitong capsules to evaluate the safety of Yaobitong in patients with acute LDH.

This study is a large sample multi-center randomized controlled trial, but there are limitations: the blinding is not implemented for participants and outcome assessors in this trial, which may produce potential bias factors. The statisticians who pool all results will be blinded throughout this trial, which may effectively reduce bias. The conclusions of this trial will provide the decision maker with valid information concerning the effect and safety of Yaobitong capsules in patients with acute LDH.
